# 6.0 Patient Monitoring and Criteria for Withdrawal from Study

**6.1 Patient monitoring**

Monitoring will be performed by the principal investigator and study team. During the treatment and post treatment follow up periods, a review of the patient’s medical history will be performed at the NIH at each scheduled follow up visit and either a complete or targeted physical exam (Table 1). After screening and prior to signing the standard consent, patients will undergo a complete physical exam by a staff physician. Additionally, they will undergo a complete physical exam by a staff physician on Days 29 and 43. On Days 1, 15 and 64, targeted physical exams will be performed as clinically indicated. Evaluations will also take place more frequently as clinically indicated. Laboratory monitoring at these visits will include the following:

- CBC with differential, acute care panel, hepatic and mineral profiles, amylase, lipase, PT and PTT, urinalysis, and urine pregnancy testing (if appropriate)
- CD4+ and CD8+ T cell counts
- HIV plasma viral load
- Expression of Ki67, CD25, HLA-DR, CD38
- Memory/naïve phenotyping of lymphocytes
- A77 1726 level

Blood will be obtained for additional research purposes. Studies to be done include the following:

- ELISA for IL-2, IL-7, TNF serum levels
- Lymphoproliferative responses
- Annexin V staining
- *Ex vivo* BrdU

6.2 A77 1726 levels

During the treatment and follow up period, blood will also be obtained for measurement of A77 1726, the main metabolite of leflunomide. These levels will be used to correlate with primary and secondary endpoints as well as to assure complete clearance of the metabolite at the end of the elimination procedure. The levels will be measured by Labcorp Clinical Trials Department. Levels that are drawn during the treatment period will be stored and run in batches so as not to unblind patient treatment arms. However, the level that is drawn following the elimination procedure will be measured in real time so that a decision can be made as to whether that patient will need to repeat the elimination procedure.

**6.3 Criteria for stopping study drug and immediate institution of drug elimination procedure**

If a patient meets any of the following criteria for stopping study drug, his dosing assignment will be unblinded and if he was receiving leflunomide, he will be started immediately on the drug elimination procedure:

1. Patient develops malignancy or serious infection
2. Patient becomes pregnant
3. Patient develops elevation of liver enzymes greater than 2X the upper limit of normal (if liver enzymes are 3 X the upper limit of normal the study drug will be stopped immediately; if liver enzymes are >2 but <3 X the upper limit of normal, they will be repeated in 24 to 72 hours and if they remain >2 X the upper limit of normal the study drug will be stopped)
4. Patient develops grade III or IV adverse event or toxicity
5. Patient develops grade II or greater allergic reaction or urticaria
6. Patient develops a drop in CD4+ T cell count of 40% of baseline or a CD4+ T cell count of <200 that is confirmed with a second measurement (after 10-14 days) [Baseline CD4+ T cell count = average of CD4+ T cell count at H&P and Day 1]
7. Patient develops a medical condition that in the opinion of the investigator indicates that discontinuing the study drug is in the subject’s best interest

Additional criteria for stopping study drug:

1. It is felt by the principal investigator to be in the patient’s best interest, even if the patient does not agree
2. The patient begins taking any of the contraindicated medications listed in Appendix A or B or any other medication listed as an exclusion criteria and does not agree to discontinue it
3. The patient begins taking antiretroviral medications
4. Patient desire to leave study
5. Patient noncompliance
6. Termination of study

At the time of withdrawal from study, a member of the study team (the study coordinator, principal investigator, associate investigator or covering physician) will contact the pharmacy for unblinding of treatment arm (PDS during business hours Monday through Friday or inpatient pharmacy after hours and on weekends). If a patient was receiving leflunomide, oral cholestyramine 8 g three times daily will be administered for a total of 11 days. Serum A77 1726 level will be measured upon completion of this procedure. If the A77 1726 level is above 0.02 mg/L, the elimination procedure will be repeated.

In addition, safety and research labs will be performed as at other clinic visits. Any other testing will be performed as clinically indicated.

If a patient ends study due to a drop in CD4+ T cell count, the patient’s CD4+ T cell count will be monitored following the leflunomide elimination procedure. If the CD4+ T cell count remains decreased 10 – 14 days after the elimination procedure is completed, the patient will be referred to their primary care physician for further monitoring and consideration of treatment with antiretrovirals, depending on their actual CD4+ T cell count and viral load.

If patients withdraw from study prior to receiving study drug, they will be replaced by enrolling new patients in their place. This refers only to patients who withdraw prior to receiving study drug and whose treatment arm has not been unblinded to either the subject or the study team.

If a patient withdraws from study for any reason, every effort will be made to attain complete data from that patient, including endpoint data at Day 29.

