**4.4.2 Treatment period (Day 1 through 28)**

Patients must have stopped taking contraindicated medications one week prior to Day 1 (see Appendix A - Medications Metabolized by CYP 2C9 and Contraindicated During Treatment Period). Day 1 through 28, patients will receive leflunomide 20 mg orally, once daily or placebo. If appropriate, a urine pregnancy test will be performed on Day 1 before delivery of study drug.

On Days 1 and 15 of study, patients will return for clinic visits (it will be sufficient if patients come within plus or minus 2 days of each study visit during the treatment period and within plus or minus 7 days during the post-treatment follow up period). At these visits their history will be reviewed and they will undergo a targeted physical exam to be driven by any signs or symptoms identified by the patient. The targeted physical exam will also include temperature, pulse, blood pressure, respiratory rate and examination of the heart, lungs and abdomen. Patients will have urine sent for pregnancy testing if appropriate and blood drawn for safety labs, HIV viral load, CD4+ and CD8+ T cell counts, expression of Ki67, expression of activation markers, memory/naïve phenotyping, expression of coreceptors (CCR5 and CXCR4), ELISA for IL-7, TNF level, lymphoproliferative responses, Annexin V staining and *ex vivo* BrdU. Additionally, blood will be drawn for measurement of the main metabolite of leflunomide, M1 or A77 1726. On Day 1, blood will be drawn for these labs prior to administration of medication so that these values will serve as baseline values.

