**4.4.3 Post-treatment follow up period (Day 29 through 64)**

On Day 29, the patient’s treatment arm will be unblinded. Patients who were receiving placebo will end study on Day 29. Patients who were receiving leflunomide will begin the drug elimination procedure: cholestyramine 8 grams orally three times a day for 11 days over the following 14 days. On Day 43, a serum A77 1726 level will be measured to assure elimination of the drug metabolite from the serum. Drug level should be less than 0.02 mg/L (or 0.02 ug/mL). If A77 1726 is less than 0.02 mg/L, the patient will end study on Day 64. If the level is above 0.02 mg/L, the 11 day cholestyramine elimination procedure will be repeated, and the study period will be extended as needed.

During the post-treatment follow up period, patients will come in for study visits on Days 29, 43 and 64. On these days, they will have their histories reviewed, urine will be sent for pregnancy testing when appropriate, and blood will be drawn for safety labs, HIV viral load, CD4+ and CD8+ T cell counts. On Days 29 and 43, blood will also be drawn for research studies of lymphocytes including expression of Ki67, expression of activation markers, memory/naïve phenotyping, expression of coreceptors (CCR5 and CXCR4), ELISA for IL-7, TNF level, lymphoproliferative responses, Annexin V staining and *ex vivo* BrdU as well as for measurement of A77 1726. On Days 29 and 43 they will undergo comprehensive physical exams and on Day 64 a targeted physical exam.

Table 1. Procedures

|  | Scr | H&P | D11 | D15 | D29 | D432 | D642 |
| --- | --- | --- | --- | --- | --- | --- | --- |
| Screening consent | X |  |  |  |  |  |  |
| Standard consent |  | X |  |  |  |  |  |
| History | X | X | X | X | X | X | X |
| Comprehensive physical exam |  | X |  |  | X | X |  |
| Targeted physical exam |  |  | X | X |  |  | X |
| EKG and CXR | X |  |  |  |  |  |  |
| HLA testing | X |  |  |  |  |  |  |
| Safety labs3 | X | X | X | X | X | X | X |
| Urine pregnancy test4 | X | X | X | X | X | X | X |
| HIV ELISA5 | X |  |  |  |  |  |  |
| Hep B, C serology6 | X |  |  |  |  |  |  |
| Lipid panel | X |  |  |  |  |  |  |
| HIV viral load | X | X | X | X | X | X | X |
| Flow cytometry | X7 | X7 | X8 | X8 | X8 | X8 | X7 |
| Additional studies9 |  |  | X | X | X | X |  |
| A77 1726 level |  |  | X | X | X | X |  |

1. On Day 1, blood will be drawn prior to administration of study drug

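### In Appendix D, the Grade 4 limits for hypercalcemia and hypomagnesemia carry units that contradict their own rows, and these grades feed a stopping criterion

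*Protocol*

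**What the plan says.** Section 6.3 lists the events that stop study drug, unblind the patient and, on leflunomide, start cholestyramine at once. Criterion 4 is "Patient develops grade III or IV adverse event or toxicity". Section 7.2 takes the grades from Appendix D, and Section 7.2.1 sends Grade 3 and 4 events to the IRB within 3 days. Calcium and magnesium belong to the mineral panel (Section 4.4.1), which Table 1 schedules at every visit.

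Appendix D gives these bands:

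- Hypercalcemia: Grade 1, 2.65 to 2.875 mmol/L; Grade 2, 2.9 to 3.125 mmol/L; Grade 3, 3.15 to 3.375 mmol/L; Grade 4, >3.375 **mg/dL**.
- Hypomagnesemia: Grade 1, 0.6 to 0.7 mmol/L; Grade 2, 0.45 to 0.55 mmol/L; Grade 3, 0.3 to 0.4 mmol/L; Grade 4, <0.3 **meq/L**.
- Hypocalcemia: mmol/L throughout, with Grade 1 at 1.95 to 2.04, Grade 2 at 1.75 to 1.925, Grade 3 at 1.525 to 1.725 and Grade 4 at <1.525.

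For the secondary comment, criterion 6 acts on a 40% fall in CD4 count, or a count below 200, "that is confirmed with a second measurement (after 10-14 days". Section 4.4.2 says "Day 1 through 28, patients will receive leflunomide 20 mg orally, once daily or placebo" and "On Days 1 and 15 of study, patients will return for clinic visits", with attendance allowed "within plus or minus 2 days of each study visit during the treatment period".

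**The concern.** A grading table that triggers a stopping rule should give each value one grade, and a worse value should never get a lower grade than a milder one. These two rows fail that test as written. The hypercalcemia cell puts normal values in the most severe grade. The hypomagnesemia cell leaves ungraded a range that is worse than one that already stops drug. The same grades drive expedited IRB reporting, and through Section 6.3 they can contribute to the urgent DSMB trigger in Sections 6.4 and 8.1. So these are decision thresholds, not background text.

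The bands also do not meet at the Grade 2/3 boundary, which is where criterion 4 starts to apply.

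The CD4 criterion raises a different question: whether its confirmation interval fits a 28-day course. Under the same list, raised liver enzymes are repeated within 24 to 72 hours.

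**Working it through.** The protocol gives no calculation on this point, so there is no stated figure to reproduce. The conversions are standard and not taken from the documents: calcium 1 mmol/L = 40.08/10 = 4.008 mg/dL; magnesium is divalent, so 1 mmol/L = 2 meq/L.

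**Hypercalcemia, Grade 4**

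- As printed: 3.375 mg/dL / 4.008 = 0.84 mmol/L.
- The table's own ungraded calcium range lies between Grade 1 hypocalcemia (up to 2.04) and Grade 1 hypercalcemia (from 2.65), about 2.05 to 2.64 mmol/L. In mg/dL that is 2.05 × 4.008 = 8.2 to 2.64 × 4.008 = 10.6. All of it exceeds 3.375 mg/dL, so all of it is literally Grade 4.
- In the row's own unit: 3.375 mmol/L × 4.008 = 13.5 mg/dL, which follows on directly from Grade 3.
- The error is one of over-inclusion. A calcium truly above 3.375 mmol/L also exceeds the printed limit, so no severe case is missed.

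**Hypomagnesemia, Grade 4**

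- As printed: 0.3 meq/L / 2 = 0.15 mmol/L.
- 0.35 mmol/L is Grade 3 and stops drug.
- 0.20 mmol/L is 0.20 × 2 = 0.40 meq/L. That is not below 0.3 meq/L, and it is below the Grade 3 band, so it has no grade.
- 0.10 mmol/L is 0.20 meq/L, which is Grade 4.
- So 0.15 to <0.30 mmol/L is ungraded. Here the error is one of omission. In the row's own unit, <0.3 mmol/L (0.6 meq/L) adjoins Grade 3.

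**Hypocalcemia, Grade 4**

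- Grades 3 and 4 meet at 1.525 mmol/L in the same unit. This cell is correct.

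**Gaps between Grade 2 and Grade 3**

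- Hypocalcemia: between 1.725 and 1.75 mmol/L (width 0.025; 0.025 × 4.008 = 0.1 mg/dL).
- Hypercalcemia: between 3.125 and 3.15 mmol/L (width 0.025; 0.1 mg/dL).
- Hypomagnesemia: between 0.4 and 0.45 mmol/L (width 0.05; 0.05 × 2 = 0.1 meq/L).

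**Secondary: timing of the CD4 confirmation**

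- Day 1 is pre-dose: "On Day 1, blood will be drawn for these labs prior to administration of medication so that these values will serve as baseline values". The only scheduled count during dosing is therefore Day 15, and the next is Day 29.
- Confirmation day = 15 + 10 to 15 + 14 = Day 25 to 29. With the visit window it is 13 + 10 to 17 + 14 = Day 23 to 31.
- Last dose: Day 28. At Day 25, 28 − 25 = 3 doses remain after that day, or 4 counting it. At Day 23, 5 remain, or 6 counting it. At Day 29 or later, none remain.
- On Day 29 the protocol acts anyway: "Patients who were receiving leflunomide will begin the drug elimination procedure".

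**The case against.** The strongest reply on the units is that nobody would be misled. Each Grade 4 number equals the adjoining Grade 3 limit (3.375 and 0.3), and the calcium and magnesium rows are marked as adapted to the local laboratory's values, so the intended unit is plain. Staff would not grade a normal calcium as Grade 4; Section 7.1 in any case requires an adverse event to be unfavorable and either new or worse than at baseline. A magnesium just under 0.3 mmol/L would very likely be treated at least as seriously as the Grade 3 value beside it. Criterion 7 also lets the investigator stop drug for a medical condition whatever its grade. All of this stands, and it limits the practical effect. It does not make the printed thresholds right.

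The gaps are also fairly called small. Each is 0.1 in conventional units, which suggests adjoining one-decimal bands that were converted. Whether a result can fall inside a gap depends on the laboratory's reporting resolution, which the protocol does not give.

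A reader might infer more than the protocol supports, in three ways:

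- That two Section 6.3 stopping rules cannot work. Criterion 4 works for the other rows of Appendix D. Criterion 6 can still avert a few doses, and Day 15 is only the scheduled count, since "Evaluations will also take place more frequently as clinically indicated". The investigator may also stop drug without a confirmed fall. A confirmed fall further leads to CD4 monitoring after elimination and, if the count stays low, to referral (Section 6.3).
- That calcium grading is wrong as a whole. Only the Grade 4 hypercalcemia unit is wrong.
- That severe magnesium values would in fact escape the stopping rule. That follows only if staff apply the printed unit literally.

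**Conclusion.** The point holds as a correction to two decision thresholds. Hypercalcemia Grade 4 is set about fourfold too low (0.84 instead of 3.375 mmol/L). Hypomagnesemia Grade 4 is set at half the evident limit (0.15 instead of 0.3 mmol/L), which leaves 0.15 to <0.30 mmol/L ungraded. Both reach criterion 4 and IRB reporting. The conclusion assumes that each intended limit is the printed number in the row's own unit, which the shared Grade 3/4 boundary supports. The likely effect in practice is limited, and the primary endpoint, sample size and analysis are untouched.

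The CD4 timing is a secondary comment only. On the scheduled visits, confirming a Day 15 fall averts at most 3 or 4 of 28 doses (5 or 6 at the edge of the visit window), and none if confirmation waits for Day 29. During dosing the criterion therefore adds little beyond investigator discretion and unscheduled counts. How long to wait before confirming a CD4 fall is a clinical trade-off, and the protocol gives no basis for naming a different interval here.

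**What to change.** In Appendix D, change hypercalcemia Grade 4 to >3.375 mmol/L and hypomagnesemia Grade 4 to <0.3 mmol/L. Leave hypocalcemia Grade 4 as it is.

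Make Grades 2 and 3 contiguous. One way, which puts the in-between values in the grade that stops drug, is hypercalcemia Grade 3 at >3.125 to 3.375, hypocalcemia Grade 3 at 1.525 to <1.75, and hypomagnesemia Grade 3 at 0.3 to <0.45 mmol/L. Assigning them to Grade 2 would also close the gaps; the sponsor should choose one and state it.

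This costs amendment wording only, with no added visits or tests.

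Optionally, the sponsor's clinicians may reconsider whether the 10 to 14 day interval in criterion 6 suits a 28-day course with one scheduled on-drug count. A shorter interval would cost at most one unscheduled CD4 count in a patient who triggers the rule.

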6.4 Criteria for stopping enrollment

A Data Safety Monitoring Board (DSMB) will meet at a predetermined time (when 8 subjects have completed the 28 day active treatment phase) as well as on an urgent basis if 2 or more patients meet criteria for stopping study drug due to adverse events that are possibly, probably, or definitely related to the study drugs. This board will review safety data and determine whether the study should continue enrollment and/or study drug dosing. If enrollment is closed and the study terminated, the dosing arm of those patients who are enrolled at that time and receiving the study drug will be unblinded. As soon as possible, a member from the pharmacy will inform the study coordinator of the patient’s treatment arm, and the study coordinator will inform the patient. Those patients who had been receiving leflunomide will undergo the drug elimination procedure.

**7.0 Adverse Event Reporting**

**7.1 Definitions**

Adverse events (AE): Any unfavorable and unintended diagnosis, symptom, sign (including an abnormal laboratory finding), syndrome or disease which either occurs during the study, having been absent at baseline, or if present at baseline, appears to worsen.

Serious adverse events (SAE): Any untoward medical occurrence that

- 1. results in death
  2. is life-threatening
  3. requires hospitalization or prolongation of existing hospitalization
  4. results in disability/incapacity
  5. results in congenital anomaly/birth defect
  6. other situations such as important medical events (eg. diagnosis of cancer) that may not be immediately life-threatening or result in death or hospitalization but may jeopardize the subject or may require medical or surgical intervention to prevent one of the other outcomes listed above

Unexpected adverse event: An adverse event that is not described in the package insert or current literature with regards to leflunomide or cholestyramine

Relationship assessment: The relationship between a serious adverse event and study drug is determined by the principal investigator. The degree of certainty about causality is graded as follows:

- Unrelated: adverse event is clearly due to extraneous causes
- Unlikely (must have two): adverse event:
  - Does not have temporal relationship to intervention
  - Could readily have been produced by the subject’s clinical state
  - Could have been due to environmental or other interventions
  - Does not follow known pattern of response to intervention
  - Does not appear to worsen with reintroduction of intervention
- Possible (must have 2): adverse event:
  - Has a reasonable temporal relationship to intervention
  - Could not readily have been produced by the subject’s clinical state
  - Could not readily have been due to environmental or other interventions
  - Follows a known pattern of response to intervention
- Probable (must have 3): adverse event
  - Has a reasonable temporal relationship to intervention
  - Could not readily have been produced by the subject’s clinical state or have been due to environmental or other interventions
  - Follow a known pattern of response to intervention
  - Disappears or decreases with reduction in dose or cessation of intervention
- Definite (must have all 4): adverse event
  - Has a reasonable temporal relationship to intervention
  - Could not readily have been produced by the subject’s clinical state or have been due to environmental or other interventions
  - Follows a known pattern of response to intervention
  - Disappears or decreases with reduction in dose or cessation of intervention

## **7.2 Reporting**

Adverse events: Expected adverse events are those listed in the package inserts for leflunomide and cholestyramine. Adverse events, as well as degree of relationship to study drug, will be entered into a database system; for this system they are graded according to the AIDS Clinical Trial Group (ACTG) Toxicity Table (See Appendix D). For abnormalities NOT found elsewhere on the Toxicity Table they will be assessed for severity:

- Grade 1: Transient or mild discomfort; no limitation in activity; no medical intervention/therapy required.
- Grade 2: Mild to moderate limitation in activity - some assistance may be needed; no or minimal medical intervention/therapy required.
- Grade 3: Marked limitation in activity, some assistance usually required; medical intervention/therapy required, hospitalization possible.
- Grade 4: Extreme limitation in activity, significant assistance required; significant medical intervention/therapy required, hospitalization or hospice care.

7.2.1 Reporting to the IRB

The following types of serious adverse events, regardless of relationship to study drug, will be reported to the IRB by fax or phone within 24 hours of awareness of the event followed by written SAE form within 3 days of awareness of event:

- Death
- Life-threatening event
- Cancer occurring on study
- Pregnancy
- Congenital anomaly/birth defect
- Permanent disability/incapacity

The following types of serious adverse events will be reported to the IRB by written SAE form within 3 days of knowledge of the event:

- Grade 3 and 4 adverse events
- Hospitalizations
- Adverse events of any toxicity considered serious by the principle investigator
- Any other event or condition which in the judgment of the principle investigator represents a significant hazard

The following types of adverse events will be reported to the IRB at annual review of the protocol:

- Grade 2 adverse events except those determined to be unrelated or unlikely to be related to study drug (Grade 3 and 4 adverse events will be reported as described above)

7.2.2 Reporting to the sponsor

NIAID is the sponsor for the Investigational New Drug (IND) application filed at the US Food and Drug Administration (FDA). In accordance with the Code of Federal Regulations (CFR), the IND sponsor and investigators participating in a clinical trial are responsible for the proper reporting of serious adverse events (SAEs). The purpose of reporting SAEs is to better understand the toxicity and safety of investigational agents. SAE reporting and monitoring also assist in alerting the FDA, sponsor, and clinical investigators of real and potential patient safety issues. NIAID must report SAEs that are serious, unexpected, and related to the study drug to the FDA in the form of a written IND Safety Report. In general, IND Safety Reports must be submitted to the FDA as soon as possible, but no later than 15 calendar days after the sponsor is notified of the SAE. Deaths and life-threatening events with any possible relationship to a study drug must be reported to the FDA within 7 calendar days of the sponsor’s awareness.

All deaths and life-threatening SAEs will be reported to Regulatory Compliance and Human Subjects Protection Branch (RCHSPB) Safety Department within 1 business day, and all other SAEs will be reported within 3 business days. The Safety Department can be contacted by phone at [contact], by fax at [contact], and by email at [[contact]](mailto:[contact]). RCHSPB will report SAEs for the FDA in accordance with 21 CFR 312.

